#### Anxiety and depression

At the T1-T6 visits, the PROMIS Depression-Short Form 4a [54] (Coefficient alpha > 0.90) will be used to assess depressive symptoms, with four questions (e.g., sadness and hopelessness over the past week) rated on a 5-point Likert scale ranging from 1 (Never) to 5 (Always). The total score ranges from 4 to 20, with higher scores indicating greater depressive symptoms. Also, at the T1-T6 visits, the valid and reliable (Cronbach’s a> 0.90) PROMIS Anxiety-Short Form 4a [54] will be used to assess anxiety symptoms over the past seven days. Four items (i.e., feeling uneasy) are rated from 1 (Never) to 5 (Always), with the total score ranging from 4 to 20.

#### Sleep related problems

Two instruments will be administered at visits T1 to T6 to capture sleep related problems. The PROMIS SF–Sleep Disturbance 4a [55] collects 4 items (e.g., difficulty falling asleep) on a 5-point scale (very poor to very good), with a total raw score ranging from 8 to 40. The Sleep Related Impairment 4a collects 4 items on a 5-point scale (not at all to very much), with a total raw score also ranging from 8 to 40. The raw scores for both of these are rescaled into a standardized T-score with a mean of 50 and a standard deviation of 10. Higher scores indicate a greater severity of sleep disturbance.

#### Physical function, fatigue, and pain interference

These measures will be captured at visits T1 to T6. The PROMISE SF-Physical Function 4a [56] collects 4 items (e.g., ability to do chores) on a 5-point scale (without any difficulty to unable to do), with a total score ranging from 4 to 16. The PROMISE SF-Fatigue 4a [57] collects 4 items (e.g., trouble starting things because tired) on a 5-point scale (not at all to very much), with a total score ranging from 8 to 40. The PROMISE SF-Pain Interference 4a [58] collects 4 items (e.g., how much pain interfered with chores) on a 5-point scale (not at all to very much), with a total score ranging from 6 to 30.

#### Difficulty participating socially

At visits T1 to T6, the 4-item PROMISE SF-Ability to Participate Social 4a [59] will be used to assess difficulty participating in social activity. The questions (e.g., trouble doing activities with friends) are answered on a 5-point scale (never to always) with a total raw score ranging from 4 to 20.

### Air pollution data

We will measure PM_2.5_ using two U.S. Environmental Protection Agency monitors, one located in one agricultural study community just south of Lake Okeechobee and one located in the reference community east of the main study region (Figs 1–4). Due to the dynamic nature (i.e., stochastic) of smoke plumes and air pollution dispersion from agricultural fires, we will also install 36 low-cost PurpleAir sensors placed in the study area by the CSU team and the community research assistants. We will ensure the air sensors are installed at residences located in majority Black/Hispanic and majority non-Hispanic White neighborhoods, according to Census data. PurpleAir monitors provide estimates of PM_2.5_ by mass using the Plantower PMS5003 laser particle counter, which does not have the accuracy of the EPA AQS monitors. To approximate the EPA monitoring data, we (1) apply the Plantower PM_2.5_ correction factors from Barkjohn *et al*. (2021) [60] and (2) temporally bias-correct Plantower PM_2.5_ measurements using closely located PurpleAir and EPA monitors. PurpleAir monitors are also equipped with a BOSHC BME280 to measure environmental factors (i.e., temperature, pressure, relative humidity).

All PurpleAir data from study-specific monitors are available for download through the PurpleAir Data Download Tool. Though there are not extensive publicly operating PurpleAir monitors in the study area, there are several PurpleAir monitors that operate east of the study area closer to the Atlantic coast, which in prior study campaigns (Sablan *et al*. 2024) [44] have been used to compare to data collected as part of our study. As of 2023, PurpleAir charges for data download for publicly operating monitors using a point-based billing system. Points range in value (100,000 to 1,000,000 per USD) depending on how many are purchased. The cost of data on a point basis depends on the data fields and number of observations requested. Based on prior work, the research team will leverage recently developed high-resolution fire-detection and Aerosol Optical Depth (AOD) products from NASA’s Moderate Resolution Imaging Radiospectrometer (MODIS), NOAA’s Visible Infrared Imaging Radiometer Suite (VIIRS), and the Geostationary Operational Environmental Satellite (GOES-16) to develop local climatologies of fire and smoke. This procedure leverages NOAA’s Hazard Mapping System (HMS) satellite-based observations to separate smoke from non-smoke influence. We will create daily kriged surfaces of bias-corrected PM_2.5_ for each study community for baseline and subsequent study years. Participants will be assigned exposures based on their home location. Based on daily estimates of PM_2.5_, we can aggregate the observations at any temporal resolution, including hour, day, week, month, and burn and non-burn seasons, to form the exposure assessment strategy for Aim 1.

### Neighborhood social and built environment variables

Neighborhood social and built environments at the residential Census block group level will be captured with 4 domain indices (green environment, neighborhood socio-economic status, social environment, walk-friendly design) and a summary Healthy Neighborhood Index (HNI). Domain categories were determined *a priori* as they are major neighborhood-level constructs associated with ADRD risk factors and disease risk in prior studies (citations). These measures will be calculated for the baseline visit year and following years, accounting for changes in residential address and changes in neighborhood environments, as applicable. ArcGIS Pro will be used to calculate and map these objective geographic information systems (GIS) measures.

### Green environment

Percentage of tree canopy: Tree canopy data obtained from the U.S. Forestry Service will be used to calculate the percentage of the block group comprised of tree canopy (i.e., percentage of tree coverage of the ground provided by tree leaves, branches, needles, and stems).Mean normalized difference vegetation index (NDVI) will be calculated for each participant’s neighborhood for the burn and non-burn periods based on satellite imagery available from the U.S. Geological Survey (USGS, Landsat 8 Level 2, Collection 2, Tier 1). The NDVI scale is -1 to +1 (more positive measures = healthier vegetation/”greener”) and is calculated as follows: NDVI = (R_NIR_-R_RED_)/(R_NIR_+R_RED_). R_NIR_ is reflectance in near-infrared (0.86–0.88mm) and R_RED_ is reflectance in red (0.64–0.67mm). Reflectance values are captured in 30x30 meter Landsat satellite images. Mean NDVI will be calculated for participants’ Census block group. This global measure of the density of healthy vegetation captures all types of greenery including purposefully-built greenspaces (e.g., park/open spaces, street plantings, and yards) and those in natural and rural environments (e.g., forests, farms, and uninhabited areas), and has been linked to multiple ADRD risk factors and outcomes.Percentage open space: National Land Cover Dataset (NLCD) will be acquired through the Multi-Resolution Land Characteristics Consortium, to calculate the percentage of open space in the block group. The NLCD uses 30-meter spatial resolution satellite imagery to characterize land and surface uses and types, such as developed land, barren land, deciduous forest, scrub, and wetlands. Developed open space includes mostly vegetation/grasses (<20% impervious surfaces) found in parks, large family lots, planted vegetation for recreation or erosion control, and golf courses.Percentage park space, distance to nearest park, and number of parks: We will calculate the percentage of the block group comprised of park space using combined data from the Florida Geographic Data Library’s Areas of Interest layer for Florida Parks and Recreational Facilities and ESRI’s ArcGIS Online data layer “USA Parks” (covers state parks). Distance in miles from the residence to the nearest park and number of parks in the block group will be calculated based on the same park data sources.

### Neighborhood socioeconomic status

Area deprivation index (ADI): ADI values will be downloaded from the University of Wisconsin Neighborhood Atlas. ADI was calculated from 17 U.S. Census block group variables on socioeconomic status (e.g., median home values, % families below poverty level), representing income, education, employment, and housing quality. Higher scores (range: 1–100) equate to more socioeconomically deprived neighborhoods.Percentage of vacant homes, households without internet, and average monthly housing costs: Data will be obtained from the U.S. Census American Community Survey (ACS) to calculate the percentage of all housing units in the block group that are vacant and without internet, as well as the average monthly housing costs (calculated using the average of both median mortgage and median gross rent) per block group.Percentage of renter-occupied/for-rent homes and housing and transportation costs as a percentage of household income: Data will be obtained from the Center for Neighborhood Technology Housing and Transportation Index to calculate the percentage of all housing units that a rented/for-rent as well as the average housing plus transportation costs (as percentage of household income) in the block group.

### Neighborhood social environment

Crime rate: Rates of violent crimes by city and county will be downloaded from the Federal Bureau of Investigation. Violent crime includes homicide, rape, robbery, aggravated assault, property crimes, arson, burglary, larceny-theft, and motor vehicle theft.Neighborhood sociodemographics: U.S. Census American Community Survey data will be used to characterize participants’ block groups by their racial and ethnic composition (e.g., % Black/African American, % White, % Hispanic), percentage of residents who are >65-year-olds, the average household size, and the percentage of residents who are limited English speakers.The total number of churches/worship places and civil society/membership/social clubs will be calculated for each block group from parcel-level data available from the Florida Geographic Data Library (FGDL).

### Neighborhood walk-friendly environment

Walking destinations and percentage retail: The total number of walking destinations will be calculated for each block group using parcel data from the FGDL. These destinations will include any business or public space that could facilitate social interactions and that may promote neighborhood walking, for example a post office, bank, grocery store or restaurant. Percentage retail space for each block group will be calculated using data on retail parcels (e.g., supermarkets, auto sales, shopping malls, professional services, restaurants/cafeterias, department stores).Number of pedestrian or bicycle crashes per year will be determined at the city-level using University of Florida’s SIGNAL 4 Analytics program, which receives the data from the Florida Department of Highway Safety and Motor Vehicles (FLHSMV).Percentage sidewalk and crosswalk coverage: We will use the USGS National Transportation Dataset for road network data alongside high-resolution imagery taken from Google Earth Pro to manually delineate sidewalks next to roadways and crosswalks at intersections. For each block group, we will calculate the percentage of the roadways with sidewalks and the percentage of all intersections that include a pedestrian crosswalk.Maximum road speed and annual average daily traffic (AADT) data were obtained from the Florida Department of Transportation (FDOT). Mean values for maximum road speed and AADT will be calculated for the roadways within each block group.Intersection density: Intersection density measures (auto-oriented, 3-legged/4-legged pedestrian-oriented), available from the Environmental Protection Agency’s Smart Location Database, are calculated as the number of intersections per square mile within each Census block group. A higher intersection density correlates with a more walkable environment.Compact neighborhood score: The Compact Neighborhood Score will be determined for each block group from the Center for Neighborhood Technology Housing and Transportation Index data [61]. This measure highlights areas that are higher in density, mixed use, and pedestrian friendly situated closer to rail and transit stations.Transit Access Score and Transit Connectivity Index will be determined for each block group from the Center for Neighborhood Technology Housing and Transportation Index data, which covers over 200 metrics that help analyze the social and economic impact of transit (e.g., land area accessible from a block group within a 30 minute transit trip, the number of bus routes and train stations within walking distance for households in a block group, frequency of service for public transport).

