
#### Neighborhood indices

The composite Healthy Neighborhood Index (HNI) is calculated as the average of the weighted standardized scores for the four domains or sub-indices (i.e., green environment, neighborhood SES, social environment, and walk friendly) converted to a standard normal percentile. The HNI is intended to capture the multidimensional nature of neighborhood-level factors associated with ADRD risk that cannot be explained by a single variable or a group of variables within a single domain. Data normalization is essential in composite indices as the underlying variables are often measured at different scales or units of analysis. A standard z-score calculation is used to normalize the data for the HNI composite score. Since z-score standardization requires data to be approximately normally distributed, univariate analysis is performed to identify variables with a skewed distribution and the presence of outliers. Scatter plots, box plots, or the Grubbs statistical test are employed to identify outliers. Log-10, natural log, square root, or the inverse normal method are common transformations used to create a new variable as a function f(X) of the original variable. The underlying variables for each domain or sub-index are examined for directional effect, and the z-score computation is adjusted to account for those effects. Weighting the underlying variables of each sub-index is an important consideration when different variables may have dissimilar effects on the neighborhood-level ADRD risks. In this study, we derive weights from Principal Component Analysis (PCA), specifically the component loadings matrix (post-rotation) representing the total unit ratio of explained variance for each variable loaded on a component. We compute a sub-index score for each of the four domains as the average of the underlying variables z-scores. The overall HNI index score is calculated by averaging the standard normal percentile of the four sub-components. Ordinary least squares regression analysis will be performed to gauge the internal validity of the HNI, where the HNI score will be used as the dependent variable and the four sub-indices as independent variables.

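### The city-level crash count in the walk-friendly index has no population denominator; three block-group totals also mix availability with unit size, with unknown effect

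*Protocol article*

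**What the plan says.** Four inputs to the neighborhood indices are defined as plain counts:

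- Crashes, walk-friendly domain: "Number of pedestrian or bicycle crashes per year will be determined at the city-level".
- Walking destinations, walk-friendly domain: "The total number of walking destinations will be calculated for each block group using parcel data from the FGDL".
- Worship places and clubs, social environment domain: "The total number of churches/worship places and civil society/membership/social clubs will be calculated for each block group".
- Parks, green environment domain: "number of parks in the block group will be calculated based on the same park data sources".

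Other inputs carry a denominator. Intersection measures "are calculated as the number of intersections per square mile within each Census block group". Crime is described this way: "Rates of violent crimes by city and county will be downloaded from the Federal Bureau of Investigation". Canopy, open space, park space, retail, sidewalk and crosswalk inputs are percentages.

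The Neighborhood indices section describes transformations for skew, an adjustment for direction of effect, weights from principal component analysis, and standardization: "A standard z-score calculation is used to normalize the data for the HNI composite score". Domain scores follow: "We compute a sub-index score for each of the four domains as the average of the underlying variables z-scores". Under Aim 2A, the four domains and the HNI are the exposures of the primary analysis.

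**The concern.** A yearly number of crashes per city reflects two things: how risky walking and cycling are there, and how many people live there. Only the first belongs in a walk-friendliness measure. Crime, also taken at city or county level, does not have this problem because it is a rate.

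The three block-group totals raise a related question. The study enrols from four rural communities and one suburban/urban community, so block groups plausibly differ in area and population. A total over a larger unit is then not directly comparable with a total over a smaller one. These inputs fall in three of the four domains, and the domains are the Aim 2 exposures. What is at stake is whether part of an apparent environment effect reflects the size of the city or block group.

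**Working it through.** The documents give no figure to reproduce here, so the check concerns what each definition measures.

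**1. City crash count.** Let city c have population P_c and yearly per-resident crash risk r_c, so the expected count is r_c × P_c. Suppose every city has the same risk r. Then

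z(count_c) = (r·P_c − r·mean(P)) / (r·SD(P)) = z(P_c).

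The risk cancels, and the standardized input is exactly standardized population. After a log transform, log count = log r + log P_c, so the input is standardized log population. Dividing by population first gives r for every city: apart from chance there is no difference, which is the right answer in this case.

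If risks differ, a city with k times the population has the higher count unless its risk is below 1/k of the smaller city's. City populations are not given, so k is an assumption: for k = 2, 4 and 8 the thresholds are 1/2, 1/4 and 1/8. Coding more crashes as less walk-friendly is also assumed, since the direction adjustment is described only in general terms.

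**2. Does a later step remove size?** Z-scoring is linear and leaves any correlation with size unchanged. Log and square-root transforms keep rank order. Direction adjustment changes sign, and component weights change emphasis. None divides by area or population.

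**3. Block-group totals.** Write log count = log size + log density. Let the SD of log size be 1, the SD of log density be d, and their correlation be ρ. Ignoring Poisson noise,

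corr(log count, log size) = (1 + ρd) / √(1 + d² + 2ρd).

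| Assumption | Calculation | Correlation of count with size |
|---|---|---|
| ρ = 0, d = 1 | 1/√2 | 0.71 |
| ρ = −0.8, d = 1 | 0.2/√0.4 | 0.32 |
| ρ = −0.8, d = 1.5 | −0.2/√0.85 | −0.22 |

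A simulation of 50 block groups (10 in each of 5 communities, as in the sample size section) used Poisson counts with mean 10 × size × density and with size and density independent. Across log-SDs of 0.25 to 1.5 for size and 0.5 to 1.0 for density, the standardized count correlated with size at 0.23 to 0.91. At density log-SD 1.0, dividing by size brought the correlation from 0.23–0.80 to between about 0.00 and −0.11. Those results depend on independence. With ρ = −0.8, count per unit size itself correlates −0.8 with size, a stronger link than the total has in either ρ = −0.8 row above.

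**4. Dilution.** Counting listed inputs, totals are 1 of 6 in the green domain, one or two of about eight or nine in the social domain, 2 of about 11 to 13 in the walk-friendly domain, and none in the socioeconomic domain. With equal weights (an assumption), a 1-SD shift in the crash input moves the walk-friendly average by 1/13 to 1/11, or 0.08 to 0.09. The actual weights are not given.

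**The case against.** A reader might infer more: that large rural block groups will score as richer in destinations, parks and social sites, that this biases Aim 2a and the race/ethnicity interaction in Aim 2b, and that all four totals must become densities. The documents do not support this.

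- The direction is open. Sparsely settled units probably have low density as well as large area, and the table above shows that the count-size correlation can then be small or negative.
- Count versus density is partly a choice of construct: opportunities within the residential unit, or their spatial concentration. Per-square-mile figures that include farmland may follow rurality more closely than totals do.
- Parks also enter as percentage of area and as distance to the nearest park, and destinations are accompanied by percentage retail. Intersection density, the compact neighborhood score and the transit measures also feed the walk-friendly domain.
- The Neighborhood indices section expects inputs in different units, so mixed units alone are not an error.
- Neighborhood-level covariates are planned in the Aim 2 models.

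All of this stands for the block-group totals. It does not rescue the crash count. A city total is not a measure of local availability, so there is no rival construct to defend, and its natural counterpart, crime, is already a rate. Dilution limits the consequence but is no reason to keep the definition. The article states these units outright, so this is not a detail left to a fuller document.

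**Conclusion.** The crash input is badly defined as written: at equal per-resident risk it measures city population, and nothing later in the index construction corrects that. This follows from the definition and needs no assumption about the data beyond cities differing in population and crashes being coded as adverse. Its weight is modest, as one of about 11 to 13 inputs in one of four domains. The effect on the domain score, the HNI or any Aim 2 estimate cannot be calculated without populations, counts and weights.

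For walking destinations, churches and clubs, and number of parks, the conclusion is weaker. They mix availability with unit size wherever block groups differ, but the sign and size of any resulting distortion are undetermined. Bias in Aims 2a or 2b is possible and not shown. The robustness of the indices to this choice should be reported; the documents give no basis for ruling that one denominator is correct.

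**What to change.** 1. In the Neighborhood walk-friendly environment section, define the crash input as pedestrian or bicycle crashes per 1,000 residents per year, using census population for the same city, before transformation and z-scoring.
2. Prespecify a sensitivity analysis that recomputes the affected domain indices and the HNI with walking destinations, churches and clubs, and number of parks expressed (a) per square mile of block group and (b) per 1,000 residents, and refits the Aim 2 models with each. Keep the totals in the main index if the team intends availability within the unit, and say so. Distance to the nearest park stays as planned.

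The cost is one division per variable and some additional model runs, using block-group areas from the mapping work and census populations. No new data collection is needed. The crash rate will still take one value per city, so the change removes the population component but adds no variation within a city.
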